### Objectives

The Southwest Interdisciplinary Research Center at Arizona State University will work collaboratively with a long-standing community partner, Phoenix Indian Center, and an Indigenous Youth Advisory Board to advance knowledge on salient multilevel risk and protective factors for urban Indigenous adolescent vaping and to test an adapted version of *Living in 2 Worlds* (43) to prevent nicotine and cannabis vaping in urban Indigenous youth. The Specific Aims of the study are to: (1) Identify multilevel risk and protective factors for nicotine and cannabis vaping among urban Indigenous youth in order to adapt the *Living in 2 Worlds* intervention; (2) Test the efficacy of the adapted *Living in 2 Worlds* intervention for preventing initiation and reducing use of nicotine and cannabis vaping, decreasing key risk factors for vaping initiation, and increasing skills that protect against vaping; (2b) Identify implementation barriers and facilitators of *Living in 2 Worlds*; (2c) Explore racial/ethnic identity (American Indian only vs. Multiracial/ Multiethnic) as a moderator of the efficacy of *Living in 2 Worlds*; and (3) Advance the science for engaging youth throughout the research process.

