### Quantitative hypotheses

In the Aim 2 efficacy test, we hypothesize that relative to adolescents in the comparison condition (detailed below), adolescents who participate in the adapted *Living in 2 Worlds* program will: (a) be less likely to initiate nicotine and cannabis vaping; (b) have lower vaping intentions, less permissive norms for vaping, be less vulnerable to offers, and perceive fewer benefits of vaping; (c) have better strategies for resisting vaping offers, risk assessment, decision making, and connecting with cultural values; and (d) experience similar reductions in desired alcohol, cigarettes, marijuana, and inhalants use/initiation as with the original version of *Living in 2 Worlds*. In addition, we hypothesize that youth who identify American Indian only will benefit more from the *Living in 2 Worlds* intervention than youth who identify as Multiracial/ Multiethnic. This hypothesis is based on two factors. First, youth identifying American Indian only are at greater risk for substance use, and research indicates that familial substance use has a stronger influence on cigarette use among American Indian only adolescents compare to their multiracial/multiethnic counterparts (48, 49). Second, the intervention is specifically designed to align with American Indian values, beliefs, and norms—elements that may have a stronger impact on youth who feel a closer connection to these cultural foundations. Prior research has noted that Multiracial/ Multiethnic Indigenous individuals often report weak ties to their Indigenous cultures and communities (50).

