### Study measures

#### Vaping behaviors

Key vaping outcomes are modeled after the Monitoring the Future survey for youths’ self-reports of recent (last 30 days) and lifetime vaping behaviors (66). Vaping nicotine will be defined as “vaping nicotine (using a JUUL, e-cigarette, e-pen)” (66) and vaping cannabis will be defined as “vaping marijuana or cannabis (e.g., using cannabis oils or liquids, dried herbs, or a cannabis concentrate, like wax, shatter, or budder)” (67). Separate but parallel questions will assess nicotine and cannabis vaping. These items include: During the last 30 days [lifetime] have you vaped nicotine [cannabis]? On how many days (if any) during the last 30 days [lifetime] have you vaped nicotine [cannabis]? Did you first start vaping nicotine [cannabis] in the last 30 days? There is sufficient evidence of the validity of self-reports and for comparing self-reports over time (68).

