#### Sample size calculations

Sample size calculations for the main effects of the intervention were estimated from the average effect of cigarette and marijuana use in the original *Living in 2 Worlds* efficacy trial (*d* = 0.31) and through a systematic review of school-based e-cigarette preventive interventions (*d* = 0.47). With a sample size of 132 adolescents, an effect size *of d* = 0.31 can be detected with 0.80 power for a significant intervention difference assuming a Type I error rate of *d* = 0.31, *α* = 0.05, given a pretest R^2^ = 0.67 and a 20% attrition rate. Effect sizes for the moderation analysis were estimated comparing alcohol use of urban Indigenous students who self-identified as American Indian only to students who self-identified as multiracial/ multiethnic (OR = 1.41; *d* = 0.19) (48). Assumingα = 0.05, a pretest R^2^ = 0.67, and a 20% attrition rate, we will have 80% power to detect *d* = 0.19, for statistically significant moderated intervention effects with 360 urban Indigenous adolescents ages 11–14.

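### The single main-effect power statement, built on a pretest R² of 0.67, does not hold for vaping initiation

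*Protocol article*

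**What the plan says.** Sample size calculations offers one calculation for the intervention's main effects. The effect sizes "were estimated from the average effect of cigarette and marijuana use in the original" trial (d = 0.31) and "through a systematic review of school-based e-cigarette preventive interventions" (d = 0.47). With 132 adolescents, an effect of "0.31 can be detected with 0.80 power", "given a pretest R^2^ = 0.67 and a 20% attrition rate". No outcome is exempted. Under Statistical data analysis plans, the paragraph on sensitivity analyses by sex describes the study as a whole as powered for differences above d = 0.31.

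Aim 2, under Objectives, is "preventing initiation and reducing use of nicotine and cannabis vaping". Hypothesis (a), under Quantitative hypotheses, is that intervention youth will "be less likely to initiate nicotine and cannabis vaping". Vaping behaviors plans "self-reports of recent (last 30 days) and lifetime vaping behaviors": yes/no items, a count of days vaped, and the item "Did you first start vaping nicotine [cannabis] in the last 30 days". Nicotine and cannabis are analysed separately, and the link function follows the outcome's level of measurement. Phase 3 enrols 180 adolescents per arm in five schools per arm and does not restrict entry to never-vapers.

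**The concern.** A pretest R² of 0.67 means that two thirds of the outcome variance is removed by adjusting for the T1 score. That can be a sensible input for days vaped, intentions, norms or vulnerability to offers, where T1 scores differ between pupils. It cannot apply to initiation. A pupil can initiate only if he or she had not vaped that substance before T1. Within that group every pupil has the same T1 value on the item, and a constant explains none of the later variance.

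Two further features move in the same direction. The at-risk group is smaller than the retained sample by however many pupils had already vaped at T1. The outcome is also an event, so under the article's own link rule it would be modelled as binary.

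At stake is how a null result on hypothesis (a) would be read. Against a general claim of 0.80 power it would look like fair evidence of no worthwhile effect, although the design gives initiation much less power than that.

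**Working it through.** **Inputs from the article.** d = 0.31 and d = 0.47; α = 0.05 (taken as two-sided, which reproduces the stated N; one-sided does not); power 0.80; pretest R² = 0.67; attrition 20%; N = 132 for the main effect; planned N = 360, allocated 1:1.

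**Assumed, because the article gives no figure.** Share of T1 never-vapers: 100% or 75%. Control-arm initiation: 10% to 30%. No school clustering is applied at any step.

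**Step 1: reproduce the stated figure.** Per arm, n = 2(1.960 + 0.842)²(1 − R²)/d².
- d = 0.31, R² = 0.67: 53.9, so 54 per arm, 108 in total, and 108/0.8 = 135 enrolled against 132 stated. Power at 132 × 0.8 = 105.6 completers is 0.79.
- d = 0.19 with the same formula: 144 per arm, 288 in total, 360 enrolled, exactly as stated.

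The method is therefore identified and the sums are sound.

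**Step 2: set R² to 0, still on the continuous scale.** Power = Φ(d√(n/[2(1 − R²)]) − 1.96), with n = 360 × 0.8/2 = 144 completers per arm, or 144 × 0.75 = 108 if 75% are never-vapers.

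| d | R² | Never-vapers per arm | Power |
|---|---|---|---|
| 0.31 | 0.67 | 144 | 99.6% |
| 0.31 | 0 | 144 | 75% |
| 0.31 | 0 | 108 | 62% |
| 0.47 | 0 | 144 | 98% |
| 0.47 | 0 | 108 | 93% |

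For 80% power at d = 0.31 with R² = 0, the Step 1 formula gives 164 per arm, 328 completers and 328/0.8 = 410 enrolled, all of them never-vapers. That exceeds the planned 360.

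**Step 3: treat initiation as binary.** Convert d to an odds ratio by OR = exp(−dπ/√3): 0.57 for d = 0.31 and 0.43 for d = 0.47. Apply it to the control rate p₁ to obtain p₂. Then power = Φ((p₁ − p₂)/SE − 1.96), with SE = √([p₁(1 − p₁) + p₂(1 − p₂)]/n) and n = 108 per arm.

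| Control rate (assumed) | Rate at d = 0.31 | Power | Rate at d = 0.47 | Power |
|---|---|---|---|---|
| 10% | 6.0% | 20% | 4.5% | 34% |
| 15% | 9.1% | 26% | 7.0% | 47% |
| 20% | 12.5% | 33% | 9.6% | 58% |
| 30% | 19.6% | 43% | 15.5% | 74% |

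If all 144 completers per arm were never-vapers, the d = 0.31 column would run from about 25% to 54%. At 108 per arm, the 80%-power detectable drop from a 20% control rate is to about 7%.

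**The case against.** The strongest reply is about scope. The article names no primary outcome: hypotheses (a) to (d) are not ranked, and Aim 2 pairs initiation with reduced use. The effect of 0.31 comes from cigarette and marijuana use, and for frequency of use and the risk-factor scales a pretest R² is a legitimate input. All of this stands. A reader might infer that the trial's primary outcome is underpowered, or that the trial is underpowered throughout; the article supports neither. What remains is that the calculation is offered for the main effects without exception, and initiation is the whole of hypothesis (a).

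Second, R² = 0 is exact only for the same item. T1 intentions, norms or other substance use could predict initiation among never-vapers. At an assumed R² of 0.1 to 0.3, continuous-scale power for d = 0.31 is 79% to 88% with 144 per arm and 67% to 78% with 108. But the stated input is a pretest R², and the analysis plan commits only to demographic variables found unbalanced at baseline, plus school.

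Third, 132 is not the planned size. Power at 132 with R² = 0 is 36%, but the trial enrols 360, so that figure does not describe it.

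Fourth, one might model lifetime vaping in the full sample. Pupils who had vaped before T1 would raise the R², but they cannot initiate; they add no information on initiation and dilute the effect.

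Finally, detailed power tables are often left to a fuller document. This point does not rest on an omission: a calculation is printed here, and its wording covers an outcome to which its key assumption cannot apply.

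**Conclusion.** The point holds for initiation and only for initiation. The stated 0.80 power depends on a variance reduction that the same-item pretest cannot supply among T1 never-vapers. At the planned enrolment, removing it takes power for d = 0.31 from 99.6% to at most 75% on the article's own scale. On the binary scale, which the article's link rule implies, power is below 80% at both cited effect sizes for every control rate tried with 108 never-vapers per arm.

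That the R² is 0 for the same item is certain. The size of the loss is less so, because the never-vaper share and control rates are assumptions, and the two effect sizes give quite different answers. Two stronger readings should be resisted. This is not an arithmetic error, since the printed sample sizes follow from their inputs. Nor would a null initiation result be worthless: with d = 0.47 and a 30% control rate, power is 74%. Any allowance for school clustering is a separate matter and is not counted here.

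**What to change.** In Sample size calculations, state that the R² = 0.67 calculation applies only to outcomes with a varying T1 score (days vaped, intentions, norms, vulnerability to offers), and qualify the general statement in the sensitivity-analysis paragraph to match. Add power or the detectable effect for initiation as a binary outcome in T1 never-vapers of each substance, with no pretest R², over a stated range of control rates and never-vaper shares, and for both d = 0.31 and d = 0.47. Report initiation as an estimate with its confidence interval, so that a null result is not read against 80% power.

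This is a change of text. The article places registration before Phase 3, so the restated power can be settled by then. No pupils are added. The cost is a less favourable stated power for hypothesis (a). Whether to rest the main claim on a different outcome is a trade-off for the investigators, and this correction does not require it.

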### Phase 3: Randomized controlled trial (RCT) of the vaping adaptation of living in 2 worlds

#### Randomization of schools

Ten middle schools in the Phoenix metropolitan area that have a Native American Education Program will be invited to participate in the study over the course of two cohorts (one cohort per school year). The Native American Education Program is administered by the Office of Indian Education at the Arizona Department of Education with the goal of supporting academic and culture needs of Native American students in Arizona. Schools will be randomly assigned into either: (1) *Living in 2 Worlds* Intervention (5 schools; 180 adolescents; 36 per school) or (2) Comparison group (5 schools; 180 adolescents; 36 per school).

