Sensitivity analyses will be conducted to test if the direction/magnitude of results differ based upon the sex of the youth. Although the study is powered to detect differences greater than *d* = 0.31, patterns of differences can be noted for future investigation. In addition, to respond to Phoenix Indian Center’s request to evaluate the summer camp version of *Living in 2 Worlds*, we will use a one group within-group pre-posttest design with paired t-tests (for continuous variables) or a McNemar’s chi-square test (for dichotomous variables) to examine the extent of change in vaping and associated outcomes of interest from the T3 RCT survey, which will serve as the summer camp pretest, to a post-test at the conclusion of summer camp.

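### The 80% power claimed for moderation at d = 0.19 is a two-arm main-effect calculation; power for the planned interaction test is about 20% to 29% on the plan's own inputs

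*Protocol article*

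**What the plan says.** In the protocol article, Sample size calculations gives two results. The first is for the main effect: d = 0.31 with 132 adolescents. The second is for moderation. Its planning value is introduced with "Effect sizes for the moderation analysis were estimated comparing alcohol use of urban Indigenous students who self-identified as American Indian only", set against "students who self-identified as multiracial/ multiethnic (OR = 1.41; *d* = 0.19"). The assumptions and the power follow: "a pretest R^2^ = 0.67, and a 20% attrition rate, we will have 80% power to detect *d* = 0.19". The article ties that power to the moderation test and the full sample with the words "for statistically significant moderated intervention effects with 360 urban Indigenous adolescents".

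Other sections bear on this:
- Statistical data analysis plans tests moderation by interaction terms in general linear models, and by constraining the intervention path to be equal across groups in multigroup latent change models.
- Quantitative hypotheses predicts that youth identifying as American Indian only will benefit more than multiracial/multiethnic youth. Aim 2c, under Objectives, is worded as exploration.
- Randomization of schools gives equal arms, the second being "Comparison group (5 schools; 180 adolescents; 36 per school").
- On differences by sex, Statistical data analysis plans says "Although the study is powered to detect differences greater than" d = 0.31.

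**The concern.** Two things look wrong. First, 0.19 with 360 adolescents is what a comparison of two arms of 180 would detect under the stated R² and attrition. A moderation test compares the intervention effect in one identity group with the effect in the other, and that contrast is estimated much less precisely. Second, the planning value is a prognostic difference (how much the identity groups differ in alcohol use), not a difference in how they respond to the programme.

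The moderation sentence is the only stated support for enrolling 360, because the main effect is said to need 132. A directional hypothesis also rests on it. A reader who trusts the 80% will give a null interaction more weight than it can bear.

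**Working it through.** **Inputs.** From Sample size calculations: N = 360, alpha 0.05, R² = 0.67 (residual variance 0.33), 20% attrition, d = 0.19, OR = 1.41. From Randomization of schools: 1:1 allocation. Two inputs are not stated. Sidedness is taken as two-sided, since only that reproduces the 80%. The identity split is shown from 50:50 to 80:20. No clustering allowance is applied, because the stated figures are reproduced without one.

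**Step 1: reproduce the stated 80%.**
- Analysed: 360 × 0.8 = 288, or 144 per arm.
- SE of the two-arm difference: √(4 × 0.33 / 288) = 0.0677.
- Power at 0.19: Φ(0.19/0.0677 − 1.96) = 80.1%.
- Solving for N gives 144 per arm, 288 analysed, and 288/0.8 = 360.
- With one-sided alpha the result would be 87.7%, not 80%.

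The same formula at d = 0.31 gives 54 per arm, 108 analysed, and 108/0.8 = 135, within 3% of the stated 132. Both sentences therefore use the main-effect formula.

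**Step 2: source of 0.19.** ln(1.41) × √3/π = 0.189. The planning value is the odds ratio for alcohol use between identity groups, converted to d.

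**Step 3: the planned test.** The interaction is the effect in one identity group minus the effect in the other. With share p in one group and 1:1 allocation:

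SE = √(0.33 × [4/(288p) + 4/(288(1 − p))])

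This is smallest at p = 0.5, where SE = √(0.33 × 4 × (1/144 + 1/144)) = 0.135, twice 0.0677. Power is Φ(0.19/SE − 1.96). The difference detectable with 80% power is 2.80 × SE.

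| Identity split (assumed) | Power for a difference of 0.19 | Detectable difference, 80% power |
|---|---|---|
| 50:50 | 28.9% | 0.38 |
| 60:40 | 27.9% | 0.39 |
| 70:30 | 25.0% | 0.41 |
| 80:20 | 20.1% | 0.47 |

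A simulation of the 50:50 case (20,000 runs) gave 28.4%.

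**Step 4: sample size for 80% power at 0.19, 50:50.** 2.80² × 0.33 × 16 / 0.19² gives 1,148 analysed (unrounded multiplier), and 1,148/0.8 = 1,435 enrolled.

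**Step 5: favourable variations at 50:50.** With all 360 analysed, power is 34.8%. With one-sided alpha and 288 analysed it is 40.5%. With both, it is 47.0%.

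**The case against.** The best defence concerns scale. If d = 0.19 were meant as half the difference between the two subgroup effects (a standardised one-degree-of-freedom contrast, f = 0.19/2 = 0.095), the noncentrality is 288 × 0.095² / 0.33 = 7.9 and power is 80%. The sentence would then be right, but for a true difference in subgroup effects of 0.38. The article does not define d this way, and an odds ratio for alcohol use between identity groups cannot be the source of such a contrast.

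Several limits do stand:
- It is tempting to call 29% the most the trial could have. It is not a ceiling. It assumes two-sided alpha, completers only and an even split. The hypothesis is directional, and full-information maximum likelihood recovers something from incomplete cases. Step 5 shows that these variations still leave power well short of 80%.
- A reader might infer that d = 0.31 in the sex paragraph contradicts 0.19. It does not. It matches the main-effect planning value, and a study powered for 0.19 is also powered for 0.31. The text does not say that 0.31 is an interaction. Read as an effect within one sex (about 144 analysed), it would have about 90% power.
- Nothing in the article says that a non-significant interaction will be read as equal benefit. The plan to judge results by effect sizes and confidence intervals points the other way.
- Aim 2c is already exploratory, and the error leaves the efficacy estimate and its test untouched.

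**Conclusion.** The claim of 80% power at d = 0.19 for moderated intervention effects does not hold. It is exact for an overall two-arm difference and wrong for the interaction the plan will test. On the plan's R² and attrition, two-sided alpha, 288 analysed and no clustering allowance, power is about 29% at a 50:50 identity split, 25% at 70:30 and 20% at 80:20. At 50:50, a true difference of 0.19 would be missed about 71% of the time (100 − 29). Separately, and whatever formula is used, OR 1.41 is not evidence about the size of a moderation effect.

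The sex paragraph needs clarification only. If its 0.31 is meant as a difference in effects between the sexes, the detectable value at 50:50 would be about 0.38.

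Nor can 360 simply be reassigned to the main effect as it stands, because the article says 132 suffice for that. The 132 is reproduced, within 3%, with no allowance for school clustering, although schools are the unit randomised.

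**What to change.** In Sample size calculations:
- Delete the 80% power claim at d = 0.19 for moderation, together with its OR 1.41 basis.
- State the difference in subgroup effects detectable with 80% power: about 0.38 to 0.47 depending on the identity split, and larger if school clustering inflates the standard error of the interaction. Give the split assumed.
- Restate the rationale for 360 as precision for the main effect with an explicit allowance for school clustering.

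In Quantitative hypotheses and Statistical data analysis plans:
- Treat identity moderation as exploratory, in line with Aim 2c, and report the interaction estimate with its 95% CI.
- Say what d = 0.31 refers to in the sex paragraph.

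The cost is text only. The stated moderation power becomes less favourable, and no pupils are added.

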#### Implementation barriers and facilitators

Throughout the RCT implementation, outcomes of acceptability, appropriateness, utility, and fidelity of *Living in 2 Worlds* will be documented. The group facilitators who deliver *Living in 2 Worlds* will provide feedback through self-administered surveys using the Acceptability of Intervention Measures (AIM), Intervention Appropriateness Measure (IAM), and Feasibility of Intervention Measures (FIM) (63). With Phoenix Indian Center, we will assess key resource constraints (e.g., time, money, personnel, technology, and barriers related to school recruitment and program adoption) that may limit the sustainability of the intervention. Implementation fidelity will be assessed by the research team and includes adherence to program guidelines and the quantity /duration of sessions, the quality of program delivery, and the extent of participant engagement (79). Data regarding implementation fidelity will be collected by observing the delivery of *Living in 2 Worlds* curriculum lessons. Trained graduate students will conduct lesson observations at three different time points. The first observation will occur within the earliest weeks of the curriculum, and two subsequent observations will take place during core concept lessons (lessons 7 and 9). Implementation fidelity will be assessed via an instrument used successfully for fidelity measurement in the prior *Living in 2 Worlds* trial (43). Data will be analyzed to examine implementation barriers and facilitators *Living in 2 Worlds* through descriptive statistics of means and standard deviations.

